## Abstract

**Background::**

Platelet-rich plasma (PRP), an autologous platelet concentrate (contain a large number of growth factors), has been widely investigated in healing and rebuilding the bone and tendon tissue. The objective of this prospective randomized research is to study and then compare the long-term effectiveness of the repair of arthroscopic rotator cuff without and with the platelet-rich plasma. It is assumed that there is no difference in the clinical results between patients receiving the repair of arthroscopic rotator cuff and the patients who do not receive PRP enhancement.

**Methods::**

This current study is a prospective, single-center, controlled, and randomized experiment. This study was reviewed and permitted via the institutional review committee of our hospital. All the patients will receive the written informed consent in order to involve in our clinical experiment. Patients were selected from the patients who received the repair of arthroscopic rotator cuff. Patients who meet the following conditions will be included in this study: ages ranges from 18 to 55; patients with complete tear of rotator cuff confirmed during operation; the patients agreed to wear the abduction stent for 4 weeks after operation; the preoperative count of platelet count is >150,000. All patients were evaluated at follow-up and baseline for the scores of Constant-Murley (CM) and American Shoulder and Elbow Surgeons (ASES), the numerical rating scale (NRS), and retear rate. The analysis is implemented with the SPSS 16.0 (SPSS Inc., Chicago, IL), the significance level remain at *P* < .05.

**Conclusions::**

The results of this study will provide useful new information on whether PRP is effective in the arthroscopic rotator cuff repair patients.

**Trial registration::**

This study protocol was registered in Research Registry (researchregistry6108).

## Introduction

1

With the continuous development and advances of surgical instruments and technology, open technology is gradually being replaced by arthroscopic repair, which can recover faster and obtain good cosmetic results in rotator cuff repair.^[1–3]^ Nevertheless, about 27% of cases will recur.^[4]^ The insufficient tendon-bone healing is regarded to be a significant cause of recurrence. Rotator cuff retear may also be affected via a number of factors, containing smoking, the index of body mass, age, tear size, type, location, the quality of tendon, surgical technique employed, fatty infiltration, and postoperative rehabilitation.^[5,6]^ Many complementary biologic therapies have been utilized for the improvement of the early tendon healing quality, and they may also decrease the incidence of the late tendon sequelae.^[7]^

Platelet-rich plasma (PRP), an autologous platelet concentrate (contain a large number of growth factors), has been widely investigated in healing and rebuilding the bone and tendon tissue.^[8–11]^ These growth factors possess a significant effect on the regeneration, repair, and acceleration of biochemical processes, thereby reducing pain caused by the tears of rotator cuff and promoting the healing of the rotator cuff.^[12–16]^ Many systematic reviews and meta-analysis have shown that the use of the PRP in repairing the rotator cuff can not obviously improve clinical result, but it can improve the structural healing of small to moderate tears.^[17–20]^ Currently, many clinical trials, which assessed the influence of the PRP on repairing the rotator cuff, have generally reported short-term results.^[21–24]^ Therefore, the randomized controlled studies containing the long-term follow-up are critical for the evaluation of the whole latent benefits of PRP.

The objective of this prospective randomized research is to study and then compare the long-term effectiveness of the repair of arthroscopic rotator cuff without and with the platelet-rich plasma. It is assumed that there is no difference in the clinical results between patients receiving the repair of arthroscopic rotator cuff and the patients who do not receive PRP enhancement.

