### Randomization

2.3

The randomization list was generated with the block randomized procedure. Participants were randomly allocated to one of two parallel combinations to receive either PRP or placebo (with the ratio of 1:1). In order to assign participants, an independent researcher who was not participated in surgery prepared a sealed and opaque envelope, which contains the treatment task. Subsequently, an uninformed researcher opened the envelope and assigned participants to either control group or PRP group on the basis of the chose index card.

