### Sample size calculation

2.8

The power analysis was carried out previously for the determination of the size of the study sample to offer 80% statistical power at an alpha level of 0.05%. After calculation, in each group, the size of sample of 50 patients is enough to measure the difference of CM score by at least 5 points at the end of 4 years, and 10% of data may be lost. Therefore, a total of 110 participants (55 per group) are enlisted for this research.

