### Statistical analysis

2.9

The standard deviation and mean are the descriptive statistics. The normality of all the data was detected via the Kolmogorov–Smirnov test. The difference of value before and after the treatment was calculated by the paired sample *t* test. The student *t* test was applied for the comparison of variances between study group and control group. The analysis is implemented with the SPSS 16.0 (SPSS Inc., Chicago, IL), the significance level remain at *P* < .05.

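### Tear size and age are cited as possible factors in retear, but the described between-group analysis uses neither, so it gives up some precision and cannot correct an unlucky tear-size imbalance

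*Protocol article*

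**What the plan says.** In the protocol article, the Introduction says: "Rotator cuff retear may also be affected via a number of factors, containing smoking, the index of body mass, age, tear size". Tear type and location, tendon quality, surgical technique, fatty infiltration and rehabilitation complete the list. The next paragraph, summarising earlier reviews, says that PRP does not clearly improve clinical results but that "it can improve the structural healing of small to moderate tears".

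Section 2.2 requires a complete tear confirmed at operation, with no size limit, and an age of 18 to 55. Section 2.7 makes retear rate the primary outcome.

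On allocation, section 2.3 says: "The randomization list was generated with the block randomized procedure". The ratio is 1:1 and no stratification factor is named. On analysis, section 2.9 gives a paired t test for change within a group and, between groups, a Student t test that "was applied for the comparison of variances between study group and control group". I read this as a comparison of the outcome variables. No covariate or stratum appears, and no test is named for a binary outcome.

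**The concern.** Tear size has two roles in the article's background: it may predict retear, and it marks the setting in which PRP was reported to help structural healing. Age is also listed as a possible predictor. Tear size can be seen when the tear is confirmed, and age is an eligibility item, so both are available before treatment is applied. The described comparison ignores both.

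Two things are at stake. An unadjusted comparison leaves explainable variation in the error term, so precision is lost. And if one arm happens to receive more large tears, the retear difference moves for a reason unrelated to PRP, and the described analysis has no means of correcting it. The trial is run once, so a long-run average is little comfort after a bad draw.

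**Working it through.** **Inputs from the article.** 50 evaluable patients per arm (section 2.8), overall retear of about 27% (Introduction) and significance at P < .05 (section 2.9; two-sided assumed). The 50 per arm was set for a 5-point CM difference with no SD given, so it cannot be reproduced. It implies an SD of about 8.9 at two-sided 0.05. It is used here only as the size of the trial.

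**Assumptions.** The article gives no tear-size mix and no retear rate by size. I take the share of large tears, π, as 30-50%. For retear in smaller (pS) and large (pL) tears I take two main pairs with π = 40%; both reproduce 27%: 0.6 × 15% + 0.4 × 45% = 27%, and 0.6 × 11% + 0.4 × 51% = 27%. As a milder case I take 17% v 37% at π = 50%: 0.5 × 17% + 0.5 × 37% = 27%. No figure is available for age.

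**1. How often tear size is unbalanced.** The number of large tears in each arm is Binomial(50, π). Blocking on arm alone does not restrain it. The SD of the difference in share is √(2π(1−π)/50), or 9.2 to 10.0 points. Exact binomial convolution gives:

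| π | 10 or more points apart | 20 or more points apart |
|---|---|---|
| 30% | 32.6% | 3.8% |
| 40% | 35.8% | 5.2% |
| 50% | 36.8% | 5.7% |

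**2. What an imbalance does.** Shift in the retear difference = imbalance × (pL − pS). For 10 points this is 0.10 × 30 = 3 points (15% v 45%) or 0.10 × 40 = 4 points (11% v 51%). In the milder case it is 2 points. The standard error of the crude difference is √(2 × 0.27 × 0.73/50) = 8.9 points.

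**3. Precision.** The share of outcome variance explained is π(1−π)(pL−pS)²/[0.27 × 0.73].
- 15% v 45%: 0.24 × 0.09/0.1971 = 0.110; adjusted SE = 8.88 × √0.890 = 8.4 points.
- 11% v 51%: 0.24 × 0.16/0.1971 = 0.195; adjusted SE = 8.88 × √0.805 = 8.0 points.
- Milder case: 0.25 × 0.04/0.1971 = 0.051; adjusted SE = 8.7 points.

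**4. Simulation.** 400,000 trials per scenario, unstratified allocation, comparing a crude two-proportion test with a Mantel-Haenszel test by tear size. The crude test stands in for the described analysis, because a t test on a 0/1 outcome is nearly the same thing.

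| Scenario | Crude | Mantel-Haenszel |
|---|---|---|
| No effect, 15% v 45% | 5.1% | 5.1% |
| No effect, 11% v 51% | 5.1% | 5.0% |
| Risk ratio 0.4 in both strata, 15% v 45% | 56.5% | 57.9% |
| Risk ratio 0.4, 11% v 51% | 56.7% | 60.7% |
| Odds ratio 0.3 in both strata, 15% v 45% | 55.9% | 57.8% |
| Odds ratio 0.3, 11% v 51% | 51.1% | 55.8% |
| Risk ratio 0.4, milder case 17% v 37% | 56.5% | 56.3% |

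The mean difference with no effect is 0.0 points. The power gain is 1.4 to 4.7 points in the two main pairs and nil in the milder case.

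**5. The unlucky draw.** In about 2.6% of trials at π = 40%, the PRP arm has 20 or more points more large tears. With no PRP effect, the crude test then rejects in 11% (15% v 45%) or 15% (11% v 51%) of those trials. The stratified test stays at about 5%.

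**The case against.** **Chance imbalance is not bias.** A reader might infer that ignoring tear size biases the primary comparison. It does not: over repeated randomisations the mean difference is zero and type I error is about 5%. Only a distortion conditional on an unlucky allocation remains, and a 3-4 point shift is less than half of the 8.9-point standard error. This objection stands.

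**Tear size is one of about ten factors.** The article does not rank them or call tear size the main driver. Tear size is chosen here because the article also ties it to PRP's structural effect, and age because it is recorded anyway. Other choices could be defended.

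**The article is condensed.** Covariates are often left to an analysis plan, and stratification may be described in a full protocol. Section 2.3 does not say that allocation is unstratified, so no fault in the randomisation is shown. Section 2.9, however, does name its between-group test, and that stated method can be improved.

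**Dilution.** A reader might also infer that the pooled comparison is wrong because PRP is expected to work mainly in smaller tears. The sentence reports earlier reviews; the article's objective is overall effectiveness and its stated expectation is no difference in clinical results. Nor would adjustment cure dilution. If retear fell from 15% to 3% in the 60% with smaller tears and not at all in the rest, the overall difference would be 0.6 × 12 = 7.2 points, with power of about 14% crude and 15% stratified.

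**Stratified envelopes may not be cheap.** Section 2.4 prepares PRP, by blood draw and 15 minutes of centrifugation, for patients already allocated to PRP. Waiting for the tear to be sized could put allocation and preparation inside the operation. This also stands.

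**Conclusion.** The point holds in a limited form. The article cites tear size and age as possible influences on its primary outcome, and its described between-group test uses neither. The comparison remains valid on average. What is lost is about 1 to 5 points of power if retear is 11-15% in smaller and 45-51% in large tears, and about nothing if the gap is only 20 points. The described test also cannot correct an imbalance of 10 or more points in large tears, which occurs in about 33-37% of trials at 50 per arm and moves the retear difference by 3-4 points per 10 points of imbalance.

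All the stratum rates and the tear-size mix are assumptions; only the overall 27% and the sample size come from the article. The point matters less than two separate problems: the trial is sized on the CM score ("measure the difference of CM score by at least 5 points at the end of 4 years") although retear is primary, and no test for a binary outcome is named. It is still worth acting on, because prespecified adjustment is a better method than the one stated and costs almost nothing.

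**What to change.** In section 2.9:
- Record tear size, in defined categories, as seen at arthroscopy and before PRP or saline is given.
- Prespecify tear-size category and age as covariates for retear in a logistic model, or use a Mantel-Haenszel analysis by tear size.
- Include the same covariates in the models for CM, ASES and NRS.
- Report the PRP effect by tear size as exploratory only. At 60% smaller tears, that stratum has about 0.6 × 50 = 30 patients per arm.

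Keep the model small. At 27% v 10.8% retear there would be about 13.5 + 5.4 = 19 events, so two tear-size categories and one age term are about the limit.

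Stratifying the envelopes by tear size is optional, and only if it fits the timing of allocation and PRP preparation. The analysis must then stratify too: with stratified allocation, the crude test's type I error falls to 3.8% (15% v 45%) or 3.0% (11% v 51%).

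The cost is one extra recorded category, a few sentences in section 2.9 and a slightly more complex model. No extra patients or procedures are needed. If allocation has already begun, the adjustment can still be fixed before the outcome data are examined.

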## Material and method

2

### Trial design

2.1

This current study is a prospective, single-center, controlled, and randomized experiment. The study protocol was approved by the ethics committee of Changshu Hospital Affiliated to Nanjing University of Chinese Medicine (K20200927). All the patients will receive the written informed consent in order to involve in our clinical experiment. The research protocol was registered in Research Registry, with the number researchregistry6108. Between October 2020 and October 2021, our agency will evaluate 100 eligible patients.

### Participants

2.2

Patients were selected from the patients who received the repair of arthroscopic rotator cuff. Patients who meet the following conditions will be included in this study: ages ranges from 18 to 55; patients with complete tear of rotator cuff confirmed during operation; the patients agreed to wear the abduction stent for 4 weeks after operation; the preoperative count of platelet count is >150,000. Exclusion criteria include as following: patients who do not meet the inclusion criteria; previous shoulder surgery; patients with active infection, remote infection, sepsis, and osteomyelitis that may spread to surgical area; patients who are uncooperative or have a disease that prevents them from following instructions, or who do not want to come back for the follow-up examination.

### Randomization

2.3

The randomization list was generated with the block randomized procedure. Participants were randomly allocated to one of two parallel combinations to receive either PRP or placebo (with the ratio of 1:1). In order to assign participants, an independent researcher who was not participated in surgery prepared a sealed and opaque envelope, which contains the treatment task. Subsequently, an uninformed researcher opened the envelope and assigned participants to either control group or PRP group on the basis of the chose index card.

### PRP preparation

2.4

For the patients randomly divided into PRP group, the PRP was acquired with the GPS III Platelet Concentration System. In short, the PRP is prepared through taking blood (54 mL) from the patient, and then mixing the resulting blood with citrate anticoagulant (6 mL) into the disposable separation tube, afterwards, centrifuging it at 3200 rpm for 15 minutes. After the above centrifugation, the platelet-deficient plasma needs to be removed from centrifuge to generate the PRP (6 mL), the PRP is extracted and then utilized for the intraoperative injection.

### Surgical management and PRP application

2.5

All the repairs of rotator cuff were implemented by a senior shoulder surgeon under the condition of general anesthesia with a lateral decubitus position. Participants receive surgery in the beach-chair position. In all cases, plastic surgery is performed and debridement is performed at the same time, and the larger nodules are not peeled off. The simple stitches and absorbable double-load suture fixator are utilized to carry out the single-row repair. In the case of partial tear, subluxation and complete dislocation, procedures are performed on the biceps tendon. After completing the arthroscopic surgery, patients in treatment group underwent the local activation of PRP. According to the adopted scheme, the ultimate volume of PRP (6 mL) can be acquired. Through applying lateral portal, spray applicator kit equipped with the autologous thrombin and PRP syringes is placed between repaired rotator cuff and the bone with no cannula. Subsequently, inflow is closed and then the fluid under the arthroscope is carefully inhaled through outflow cannula. The PRP are then slowly injected. In control group, the patients will be given the same dose of saline in the same method.

### Postoperative protocol

2.6

The shoulder is fixed with the abduction bracket for 4 weeks. During fixation, the patients are encouraged to conduct the exercise of muscle contraction and to perform active and passive motions of the elbows, wrists, and fingers. After the patient is gradually weaned from the abduction brace from 4 to 6 weeks after surgery, further passive exercise (range of motion) and active auxiliary range of motion exercise are allowed. After 3 months, the patients begin to carry out the intensive exercises. After 3 months, jogging and other light sports are allowed, and 6 to 9 months later, the patients can fully resume exercise according to personal recovery.

### Outcomes measures

2.7

All patients were evaluated at follow-up and baseline for the scores of Constant-Murley (CM) and American Shoulder and Elbow Surgeons (ASES), the numerical rating scale (NRS), and retear rate. The primary outcome is retear rate. The NRS of people are assessed for pain on an 11-point scale ranging from zero (for “no pain”) to 10 (for “most severe pain possible”). The ASES scores and CM scores are reliable, effective and responsive, and cover various activities of daily living to assess shoulder function, and the assessment are performed at baseline, 12 months, 24 months, and 48 months.

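### The hypothesis and the sample size concern clinical results, but the declared primary outcome is structural (retear), so the primary result cannot by itself decide the hypothesis

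*Protocol article*

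**What the plan says.** All references are to the protocol article.

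- **Objective** (Abstract, Introduction, Discussion): to "compare the long-term effectiveness of the repair of arthroscopic rotator cuff without and with the platelet-rich plasma".
- **Hypothesis** (same three places): "It is assumed that there is no difference in the clinical results between patients" with and without PRP. No other hypothesis is stated.
- **Prior evidence** (Introduction): earlier reviews are reported as showing that PRP "can not obviously improve clinical result, but it can improve the structural healing of small to moderate tears".
- **Primary outcome** (section 2.7): "The primary outcome is retear rate". CM, ASES and the pain rating (NRS) are also collected but are not primary. For the two function scores, "the assessment are performed at baseline, 12 months, 24 months, and 48 months".
- **Sample size** (section 2.8): 50 per group is said to be enough to "measure the difference of CM score by at least 5 points at the end of 4 years", with 80% power. This is raised to 55 per group for 10% loss. Retear does not appear in the calculation.
- **Conclusion promised** (Abstract, Discussion): information on the effectiveness of PRP in these patients. Neither place ties effectiveness to a particular outcome.

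**The concern.** The primary outcome should be the one that answers the trial's hypothesis. Here the hypothesis is about clinical results and the primary outcome is about whether the repaired tendon stays intact. That would matter little if the two moved together, but the Introduction says that in earlier reviews they did not.

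At stake is the meaning of the main conclusion. Suppose PRP lowers the retear rate and the clinical scores are similar. The declared primary outcome then favours PRP, while the stated hypothesis of no clinical difference is not rejected. The article does not say which of these results the statement about effectiveness rests on.

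**Working it through.** **Step 1. Set the elements side by side.**

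| Element | Section | What it concerns |
|---|---|---|
| Objective | Abstract, 1, 3 | Long-term effectiveness (broad) |
| Hypothesis | Abstract, 1, 3 | Clinical results |
| Primary outcome | 2.7 | Retear (structural, yes/no) |
| Sample size | 2.8 | CM score at 4 years (clinical) |
| Analysis | 2.9 | Means, SDs, t tests (suited to scores) |

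The hypothesis and the sample size point to a clinical score, and the analysis suits one. Only the primary-outcome sentence points to retear.

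**Step 2. Could clinical results be meant to include retear?** Not in the article's own usage. The Introduction sets clinical result against structural healing in a single sentence, shortly before it states the hypothesis.

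**Step 3. List the possible patterns.**

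| Retear | Clinical scores | Primary outcome | Stated hypothesis of no clinical difference |
|---|---|---|---|
| Better | Better | Favours PRP | Rejected |
| Better | Similar | Favours PRP | Not rejected |
| Similar | Better | Does not favour PRP | Rejected |
| Similar | Similar | Does not favour PRP | Not rejected |

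Retear better appears once with the hypothesis rejected and once with it not rejected, and so does retear similar. Knowing the primary result therefore does not settle the hypothesis. The second row is the pattern the Introduction reports from earlier reviews.

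**Step 4. Which outcome does the stated power belong to?** The plan's own figure comes first. No SD is given, so the 50 per group can be neither reproduced nor refuted. Solving for the SD, with two-sided alpha 0.05 assumed (section 2.8 prints the alpha as a percentage; section 2.9 uses the usual 0.05 level):

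n = 2 (z₀.₉₇₅ + z₀.₈₀)² SD² / δ², so SD = δ / [(1.960 + 0.842) × √(2/n)] = 5 / (2.802 × 0.2) ≈ 8.9 points.

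Inflation for loss: 50 × 1.10 = 55 per group, as stated (50 / 0.90 would give 56). The calculation concerns CM only.

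**Step 5. Illustration for retear.** The article gives no control rate for the trial. I assume 27%, the recurrence figure in the Introduction, and two-sided alpha 0.05:

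power = Φ{[|p₁ − p₂|√n − 1.960 √(2p̄(1 − p̄))] / √(p₁(1 − p₁) + p₂(1 − p₂))}, where p̄ is the mean of p₁ and p₂.

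For 27% against 13.5% with n = 50: (0.9546 − 1.1139) / 0.5603 = −0.284, so power ≈ 0.39.

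| PRP retear rate | Power, 50 per group | Power, 55 per group | n per group for 80% |
|---|---|---|---|
| 20% | 0.127 | 0.136 | 575 |
| 15% | 0.311 | 0.337 | 180 |
| 13.5% | 0.388 | 0.420 | 138 |
| 10% | 0.593 | 0.635 | 81 |
| 5% | 0.862 | 0.893 | 43 |

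With 50 per group, 80% power needs a fall to about 6.4%; with 55 per group, to about 7.1%. Steps 4 and 5 show that the stated 80% cannot be carried over to retear. The mismatch between hypothesis and primary outcome rests on Steps 1 to 3 and would remain at any sample size.

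**The case against.** Several points on the other side are sound, and they limit what can be claimed.

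- **The objective is broader than the hypothesis.** Long-term effectiveness can include tendon integrity, and the Introduction motivates the trial by recurrence and poor tendon-bone healing. Retear is a defensible primary outcome for that objective. A reader might infer that the objective also conflicts with retear; the text does not support that.
- **Divergence is reported, not predicted.** A reader might infer that the protocol expects fewer retears without clinical gain in this trial. It only reports earlier reviews, limits the structural benefit to tears of small or moderate size, and notes that earlier trials were mostly short-term. Section 2.2 requires a complete tear and sets no size limit, so such tears are not excluded, but no expectation for this population or for 48 months is stated.
- **The hypothesis is not left untested.** CM, ASES and NRS are collected, CM carries the sample size, and a between-group t test is planned. The hypothesis is examined, but only through outcomes not labelled primary.
- **Discordant results need not contradict each other.** Fewer retears with similar scores answer two different questions, and one primary outcome is named in advance. Rules for reading discordant outcomes may sit in a fuller document that is not shown.
- **The point is close to the sizing mismatch.** Sizing on one outcome and declaring another primary is a related defect with much the same natural repair. It is not identical: powering the trial for retear would still leave a primary result that does not address the hypothesis.

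What stands is narrow. Hypothesis, primary outcome and sizing outcome are all printed in this article, so the mismatch is not a detail left to another document.

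**Conclusion.** The mismatch is real and should be corrected before outcome data are seen. The stated hypothesis and the sample size concern clinical results, the declared primary outcome is structural, and the article itself reports that the two have diverged under PRP. The primary result therefore cannot by itself decide the hypothesis.

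Its size is best expressed as two discordant patterns out of four, one of them already reported from earlier reviews. It would be too strong to say that the trial cannot address its hypothesis or that its conclusions fail as a whole, because the clinical data are scheduled and the trial is sized on one of the scores.

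The conclusion rests on reading clinical results as the Introduction uses the term. The retear power figures are illustrative only; they depend on the assumed 27% control rate and two-sided alpha of 0.05.

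**What to change.** **Preferred.** In section 2.7, make the between-group difference in CM score at 48 months the primary outcome, and state that the hypothesis and the conclusion on effectiveness rest on it. Report retear as a separately labelled structural outcome, and add that a retear benefit without a CM benefit will be reported as structural benefit only.

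Cost: this is a change of declared primary outcome, not just of wording. It must be recorded as a dated amendment in the protocol and the registry before outcome data are seen. No new visits or patients follow from it, since CM is already scheduled at 48 months and is the outcome used for sizing. The downside is that a retear-only benefit can no longer be claimed as clinical effectiveness.

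**If retear is kept as primary.** Restate the hypothesis in the Abstract, Introduction and Discussion in terms of structural healing, limit the primary conclusion to that, and state in section 2.8 that the 80% power applies to CM and not to retear. This costs only wording, but it leaves the primary outcome without stated power. Sizing for retear instead could need many more patients: under the 27% assumption, about 138 per group before allowance for loss to detect a halving, against 55 per group planned.
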